## Abstract

**Background:**

Multifamily group psychoeducation (MFG) has been shown to reduce relapse rates among individuals with first-episode psychosis. However, given the cognitive demands associated with participating in this intervention (e.g., learning and applying a structured problem-solving activity), the cognitive deficits that accompany psychotic disorders may limit the ability of certain individuals to benefit from this intervention. Thus, the goal of this study is to examine whether individuals with first-episode psychosis who participate simultaneously in MFG and cognitive remediation--an intervention shown to improve cognitive functioning among individuals with psychotic disorders--will be less likely to experience a relapse than individuals who participate in MFG alone.

**Methods/Design:**

Forty individuals with first-episode psychosis and their caregiving relative will be recruited to participate in this study. Individuals with first-episode psychosis will be randomized to one of two conditions: (i) MFG with concurrent participation in cognitive remediation or (ii) MFG alone. The primary outcome for this study is relapse of psychotic symptoms. We will also examine secondary outcomes among both individuals with first-episode psychosis (i.e., social and vocational functioning, health-related quality of life, service utilization, independent living status, and cognitive functioning) and their caregiving relatives (i.e., caregiver burden, anxiety, and depression)

**Discussion:**

Cognitive remediation offers the possibility of ameliorating a specific deficit (i.e., deficits in cognitive functioning) that often accompanies psychotic symptoms and may restrict the magnitude of the clinical benefits derived from MFG.

**Trial Registration:**

ClinicalTrials (NCT): NCT01196286

## Background

There is growing evidence that the majority of the psychosocial deterioration that accompanies psychotic disorders occurs during the first few years of illness [1-3] and that the prevention or delay of early deterioration may be associated with a better course of illness [4-7]. One intervention which has been shown to be particularly effective in the treatment of psychotic disorders is family psychoeducation--an umbrella term for a group of interventions that provide families with education about psychotic disorders and strategies to improve problem-solving skills and communication within the family [8]. To date, multiple studies have demonstrated that the receipt of family psychoeducation is associated with lower rates of relapse among individuals with psychotic disorders [9,10] with individuals with first-episode psychosis experiencing greater clinical benefits than individuals later in the course of a psychotic disorder [11,12].

One particular form of family psychoeducation which has shown promise among individuals with first-episode psychosis is multifamily group psychoeducation (MFG) [11]. This intervention provides participants with information about the course and treatment of psychotic disorders and trains participants in the use of a structured problem-solving exercise designed to help them navigate the many challenges associated with living with a psychotic disorder or caring for a relative with a psychotic disorder. Among individuals with psychotic disorders, participation in MFG is associated with reduced rates of relapse [13,14], and the clinical benefit of this intervention appears to be greater among individuals with first-episode psychosis as opposed to individuals with a chronic psychotic disorder [11]. The success of this intervention among individuals with first-episode psychosis has led to the incorporation of MFG within several major international studies of first-episode psychosis (e.g., OPUS [15] and TIPS [16]).

However, like all psychosocial interventions, some individuals who participate in MFG will still experience negative health outcomes. With regard to individuals with first-episode psychosis, approximately 20% may experience a symptomatic relapse and 50% may be hospitalized over a two-year period despite participating in family psychoeducation [11,13]. Thus, despite the clear clinical benefits associated with participation in MFG, there is still room for improvement with regard to the clinical outcomes of individuals who participate in this intervention.

One factor that may limit the benefit of psychosocial treatments (e.g., MFG) for psychosis is the cognitive deficits that tend to accompany psychotic disorders [17,18]. Cognitive deficits in areas such as problem-solving ability, verbal memory, and attention are common in individuals with psychotic disorders [19,20] (including those early in the course of a psychotic disorder [21,22]) and have been recognized as a "rate-limiting" factor which may hinder individuals' ability to learn and execute new skills [18,23]. In the context of MFG, these cognitive deficits may hinder an individual's ability to learn and participate in the problem-solving activity which is the hallmark of MFG. Addressing these cognitive deficits, in particular those related to problem-solving, could potentially facilitate greater participation and understanding of the MFG problem-solving activity among individuals with first-episode psychosis--thereby facilitating greater clinical benefits associated with participation in this intervention.

Recently, greater attention has been directed toward the development of strategies to ameliorate the cognitive deficits that accompany psychotic disorders. One strategy which has been shown to be successful in this endeavor is cognitive remediation (CR). This intervention, which is recognized as a "best practice" in the treatment of psychotic disorders [24,25], is typically comprised of a series of repeated exercises delivered by a clinician or via a computer that are designed to improve performance in cognitive functioning. A recent-meta-analysis has shown that participation in cognitive remediation programs is associated with improvements in multiple domains of cognitive functioning, including problem-solving ability [26]. The success of CR in improving problem-solving skills (and other areas of cognitive functioning) raises the possibility that individuals with first-episode psychosis who participate concurrently in MFG and CR may be better able to learn and apply the problem-solving activity completed during MFG sessions. This, in turn, could lead to improvements in outcomes experienced by these individuals.

Thus, the goal of this study is to examine whether concurrent participation in MFG and CR is associated with better outcomes among individuals with first-episode psychosis than participation in MFG alone. We hypothesize that relapse rates will be lower among individuals who participate in the MFG and CR condition as opposed to MFG alone. However, recognizing that the benefits of MFG and CR may not be limited to relapse alone, we will also examine the benefits of these interventions with regard to secondary outcome measures for both individuals with first-episode psychosis and their caregiving relatives.

## Methods/Design

This project was approved University of Arizona Human Subjects Protection Program.

### Participants

#### Sample Characteristics

Individuals with first-episode psychosis and their caregiving relatives will be recruited from the Early Psychosis Intervention Center (EPICENTER) at University Physicians Hospital. EPICENTER is an outpatient treatment program that provides evidence-based psychosocial treatments for individuals experiencing their first psychotic episode. Inclusion criteria for participants at EPICENTER are (i) a diagnosis of an affective or schizophrenia spectrum psychotic disorder as determined by the Structured Clinical Interview for the DSM-IV (SCID [27]), (ii) less than 5 years of frank psychotic symptoms as determined by the Symptom Onset in Schizophrenia inventory (SOS [28]), (iii) being between the ages of 18-35, and (iv) willingness to receive treatment at EPICENTER. The durational criteria for psychotic symptoms (< 5 years) is based on the operational definition of first-episode psychosis outlined by Breitborde and colleagues [29]. Individuals with first-episode psychosis are excluded from EPICENTER if they meet criteria for substance-induced psychosis as determined by the SCID, are unwilling or unable to provide informed consent, or meet criteria for a diagnosis of mental retardation. Caregiving relatives are defined as someone with whom the individual with first-episode psychosis maintains considerable face-to-face contact (≥ 10 hours per week). Family caregivers do not need to be biological relatives of the individual with first-episode psychosis. It is anticipated that some individuals with first-episode psychosis will have more than one caregiving relative who wishes to participate in the study; hence, we anticipate recruiting ≈1.5 familial caregivers for each individual with first-episode psychosis.

Given that the onset of psychosis typically occurs between the ages of 15-35 [median ≈ 22-23 years] [30], we expect that our cohort of individuals with recent-onset psychosis will comprised largely of young adults. As noted earlier, due to EPICENTER inclusion criteria, no individuals younger than 18 years old will be included in this study. As the prevalence of psychotic disorders within the United States does not appear to differ across racial or ethnic groups [31], we expect that racial and ethnic distribution of individuals with first-episode psychosis who participate in this study will be consistent with the racial and ethnic distribution of Tucson, Arizona. Per the 2000 U.S. Census data for Tucson, Arizona, this would lead us to expect that the racial distribution of our sample will be 70% White, 4% African American, 2% American Indian, 2% Asian American, <1% Native Hawaiian or other Pacific Islander, 4% multiracial, and 17% other. With regard to ethnicity, we expect that the overall sample will be comprised of 36% Hispanic/Latino individuals and 64% non-Hispanic/Latino individuals. We expect to find a similar ethnic and racial breakdown among the family caregivers who participate in this study.

First-episode psychosis studies have long reported recruiting a preponderance of male subjects [32]. Thus, we expect that our sample of individuals with first-episode psychosis will be largely male (≈70%). Conversely, studies of family caregivers of individuals with psychotic disorders have historically recruited a preponderance of female caregivers [33]. As such, we expect that our sample of caregivers will be largely female (≈70%).

#### Number of Participants and Power Analysis

Current recommendations for a priori determination of the number of subjects to include in a study suggest the inclusion of sufficient subjects to maintain adequate statistical power to detect a clinically meaningful effect size [34]. One such measure, Number Needed to Treat (NNT) [35], has been identified as particularly useful in conveying clinical significance and in guiding the design of randomized clinical trials [36]. NNT provides an estimate of the number of individuals who would need to receive a treatment in order to prevent the occurrence of one negative outcome. With regard to family psychoeducation, a recent meta-analysis found that the NTT for this intervention was 8; (95% CI 6-18) [9]. This suggests that this intervention would need to be provided to 8 individuals to prevent one relapse. Although there is no established criteria for a clinically meaningful reduction in NNT [36], for the current study we defined a clinically meaningful benefit of the MFG and CR condition as an NNT one-half the size of the NNT for MFG along (i.e., an NNT for MFG and CR = 4). This value (i.e., NNT = 4) falls outside of the 95% confidence interval of the NNT for family psychoeducation alone as reported in a past meta-analysis [9] and is consistent with the NNT value use to determine a priori statistical power for most randomized controlled trials of interventions for mental illnesses [36]. Using these NNT values and the pwr software package [37] developed for the R statistical platform [38], we determined that 17 families (i.e., individual with first-episode psychosis and caregiving relative[s]) would need to be allocated to both the MFG-CR and MFG alone conditions, respectively, to ensure statistical power of 0.80 (i.e., total sample size = 34). To protect against subject attrition, we will recruit an additional 6 families (i.e., ≈20% of the total sample size), bringing the total sample size to 40.

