### Proposed Analyses

All analyses will be completed using an "intention-to-treat" principle [68] such that data from all subjects will be included in the analysis regardless of their level of adherence to the interventions over the course of the study.

The association between intervention condition (i.e., MFG and CR vs. MFG alone) and relapse will be examined using a chi-square. However, in situations in which the requirements for this analysis are violated (e.g., expected value of any cell ≤ 5), Fisher's exact probability test [69] with the continuity correction proposed by Overall [70] will be used instead.

Per the recommendations outlined by Vickers and Altman [71], the association between intervention condition (i.e., MFG and CR vs. MFG alone) and continuous secondary outcome measures (e.g., caregiver burden and social functioning scores) will be examined using an analysis of covariance with participants' baseline scores on the secondary outcome measure included as a covariate. With regard to the association between intervention condition and categorical secondary outcome measures (e.g., employed vs. unemployed), a chi-square analysis will be used. However, in situations in which the requirements for this analysis are violated, Fisher's exact probability test [69] with the continuity correction proposed by Overall [70] will be used instead.

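### The planned primary test does not deliver the stated power of 0.80 with 17 families per arm under either reading of the NNTs of 8 and 4

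*Protocol article*

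**What the plan says.** The Protocol article, under Number of Participants and Power Analysis, takes from a meta-analysis that "the NTT for this intervention was 8; (95% CI 6-18" and defines a clinically meaningful benefit as "an NNT one-half the size of the NNT for MFG along (i.e., an NNT for MFG and CR = 4". It notes that 4 lies outside the interval 6 to 18. From these two values and the pwr package it concludes: "we determined that 17 families (i.e., individual with first-episode psychosis and caregiving relative[s]) would need to be allocated to both" conditions, "to ensure statistical power of 0.80 (i.e., total sample size = 34". Six more families are added against attrition, making 40.

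The power paragraph gives no relapse rate for either arm. The only relapse rate under family psychoeducation is in the Background: "approximately 20% may experience a symptomatic relapse and 50% may be hospitalized over a two-year period". Participation in this trial lasts 12 months.

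Under Proposed Analyses, "The association between intervention condition (i.e., MFG and CR vs. MFG alone) and relapse will be examined using a chi-square". The plan changes to another test when the chi-square requirements fail: "e.g., expected value of any cell ≤ 5), Fisher's exact probability test", with a cited continuity correction whose formula is not reproduced.

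**The concern.** An NNT is the reciprocal of a risk difference, and a risk difference fixes a sample size only together with a control rate. The article also does not say what the NNT of 4 is measured against. The 8 belongs to family psychoeducation itself, so its comparator lacks that treatment. Setting 4 beside the interval for the 8 suggests a shared scale, in which case the trial compares two arms that differ by much less than 25 points. If the 4 is instead MFG plus CR against MFG alone, the target exceeds the relapse rate quoted in the Background.

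The trial will be read as having 80% power for its primary outcome. If the true figure is far lower, a non-significant result is likely even when CR works as hoped, and could be taken as evidence that CR adds nothing.

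**Working it through.** **Inputs.** From the article: NNTs of 8 and 4; 17 per arm (34), or 20 per arm if all 40 are analysed; the chi-square/Fisher rule; about 20% relapse over two years. Assumed because not stated: two-sided 5% level; plain Fisher as the fallback; pwr's arcsine method for two proportions.

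**Risk differences.**
- Shared comparator: 1/4 − 1/8 = 0.125, a head-to-head NNT of 8.
- Head to head: 1/4 = 0.25.

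**Attempt to reproduce 17 per arm.** The arcsine method uses h = 2·asin√p1 − 2·asin√p2 and n per arm = 2(1.960 + 0.842)²/h² = 15.70/h². For n = 17, h must be √(15.70/17) = 0.961.
- 20% v 7.5%: h = 0.372, n about 113.
- 25% v 12.5%: h = 0.324, n about 149.
- 30% v 5%: n = 31.3. 50% v 25%: n = 57.3.
- 25.2% v 0.2%: h = 0.962, n = 16.95. This does give 17.
- One-sided 5%, 26% v 1%: h = 0.870, n = 2(1.645 + 0.842)²/h² = 16.3. This also gives 17.

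So the formula returns 17 for a 25-point difference only if almost nobody relapses under MFG plus CR.

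**Which test applies.** With equal arms, the expected relapse count in each arm is half the total relapses, so Fisher applies when there are 10 or fewer in all. At 20% v 7.5% with 17 per arm, about 3.4 + 1.3 = 4.7 are expected, and the probability that Fisher applies is 0.996.

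**Exact power.** All 2×2 tables were enumerated, each weighted by its two binomial probabilities, and the probability summed over tables significant under the plan's rule.

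| MFG alone v MFG plus CR | Arcsine power, 17 per arm | Plan's rule, 17 per arm | Plan's rule, 20 per arm |
|---|---|---|---|
| 20% v 7.5% | 0.19 | 0.08 | 0.11 |
| 25% v 12.5% | 0.16 | 0.08 | 0.11 |
| 20% v 0% | 0.77 | 0.24 | 0.37 |
| 25% v 0% | 0.86 | 0.43 | 0.59 |
| 30% v 5% | 0.54 | 0.35 | 0.45 |
| 50% v 25% | 0.33 | 0.31 | 0.37 |

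Over all feasible control rates:
- 12.5 points: 0.05 to 0.12 at 17 per arm; at most 0.13 at 20 per arm.
- 25 points: 0.28 to 0.43 at 17 per arm; at most 0.59 at 20 per arm.

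The two near-zero cases that reproduce 17 (25.2% v 0.2% and 26% v 1%) have exact two-sided power of 0.42 and 0.41.

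**Hand check of 20% v 0%.** With no relapses under MFG plus CR, two-sided Fisher gives 2·C(17,4)/C(34,4) = 2·2380/46376 = 0.103 for 4 v 0, and 2·C(17,5)/C(34,5) = 2·6188/278256 = 0.044 for 5 v 0. At least 5 control relapses are therefore needed, and P(Binomial(17, 0.20) ≥ 5) = 0.24. At a control rate of 25% the same probability is 0.43.

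**Against the quoted relapse rate.** 20% − 25% = −5%. If 20% were the control rate, the largest possible difference would be 20 points (NNT 5).

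**The case against.** **The software may well have returned 17.** This stands. The hypothesis is directional, sidedness is not stated, and a 25-point difference with near-zero relapse under MFG plus CR gives 17 per arm. A reader might infer a proven calculation error. The article does not support that, because the authors' call cannot be recovered. But in those cases the arcsine approximation fails (0.86 against an exact 0.43 for 25% v 0%), and the relapse rates needed are stated nowhere.

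**A 25-point difference is not ruled out.** A reader might infer that it cannot occur because the Background gives about 20%. That figure comes from other studies and the power paragraph does not adopt it. This trial rates symptoms weekly and applies its own relapse criteria, so its rate could differ. What stands is the tension: the target exceeds the only relapse rate quoted, which covers two years rather than 12 months. The power conclusion does not depend on the 20%, since the ranges cover every feasible control rate.

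**The fallback actually planned was not computed.** True, because its formula is not in the article. With mid-p as a less conservative stand-in, power at 17 per arm is still at most 0.13 (12.5 points) and 0.43 (25 points). Uncorrected chi-square, which the plan's own rule sets aside for sparse tables, reaches at most 0.17 and 0.65. With all 40 analysed its best case (25% v 0%) is 0.775, still short of 0.80.

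**Alpha and sidedness may be in the full protocol.** Agreed; their absence is not counted here.

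**Conclusion.** The point holds: the stated power of 0.80 at 17 per arm is not what the planned primary test gives under either reading of the NNTs. It is about a tenth if the NNTs share a comparator, and below one half if the 4 is head to head. Analysing all 40 families does not restore it.

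The result rests on a two-sided 5% level and plain Fisher as the fallback; the control rate was left free. A reader might infer one low figure, such as power below 0.25 in every case. That would be too strong: 0.24 belongs to 20% v 0% at 17 per arm, and the head-to-head reading reaches 0.43, or 0.59 with 40 families. Nor do the documents require the trial to be enlarged or relabelled. The defect is the power statement.

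**What to change.** In Number of Participants and Power Analysis:
- withdraw the 0.80 claim;
- say which comparator the NNT of 4 refers to, and give the resulting difference between the randomised arms;
- state the assumed 12-month relapse rate under MFG alone and reconcile it with the Background figure;
- give the exact power of the planned test, including its fallback, for 34 and for 40 families under those assumptions.

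In Proposed Analyses, report the risk difference with its 95% CI beside the test, so that a non-significant result is not read as evidence of no benefit. For scale, at 20% v 7.5% with 20 per arm the half-width is about 1.96·√(0.20·0.80/20 + 0.075·0.925/20) = 0.21. That is 21 points, wider than the 12.5-point difference itself.

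The cost is a less favourable power figure and some rewording. No extra patients are needed and the primary test is unchanged.

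### The stated power of 0.80 with 17 families per arm does not follow from the NNTs given: at two-sided 5%, a 25-point difference has exact power of 28–65% at 17 per arm and at most 77% with all 40 analysed

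*Protocol article*

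**What the plan says.** Under Number of Participants and Power Analysis, the article takes a meta-analytic NNT for family psychoeducation ("the NTT for this intervention was 8; (95% CI 6-18")) and sets the target at half of it ("i.e., an NNT for MFG and CR = 4"). It then reports the result: "Using these NNT values and the pwr software package [37] developed for the R statistical platform [38], we determined that 17 families" "would need to be allocated to both the MFG-CR and MFG alone conditions, respectively", "to ensure statistical power of 0.80 (i.e., total sample size = 34"). Six further families are added for attrition, making 40. The section gives no relapse rate for either arm and no alpha or sidedness.

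Proposed Analyses tests relapse by chi-square, with a fallback: "in situations in which the requirements for this analysis are violated (e.g., expected value of any cell ≤ 5), Fisher's exact probability test", with Overall's continuity correction. The only relapse rate in the article is in the Background, where, despite family psychoeducation, "approximately 20% may experience a symptomatic relapse and 50% may be hospitalized over a two-year period".

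**The concern.** An NNT of 4 says that two rates lie 25 points apart. It does not say where. Power for two proportions varies widely with where they lie, so two NNTs alone cannot determine 17 per arm. The number has to rest on some pair of rates, and the natural check is whether any pair makes 0.80 true for the tests the trial will use.

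Relapse is the primary outcome, and this power statement is the only justification given for the sample size. If true power is well below 0.80, a non-significant result would be quite likely even if cognitive remediation had the full effect the plan calls clinically meaningful. The article would nevertheless present the trial as adequately powered.

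**Working it through.** **Inputs.** From Number of Participants and Power Analysis: 17 per arm, 1:1, power 0.80, NNTs 8 and 4, and 40 in total (20 per arm). From Proposed Analyses: chi-square, or Fisher's test if any expected count is 5 or less (the article's example of a violated requirement, taken here as the rule). Assumed: two-sided 5%. Granted in the plan's favour: NNT = 4 is the difference between the two arms, 1/4 = 0.25. If both NNTs share one comparator, the difference is only 0.25 − 0.125 = 0.125, and power is lower still.

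**1. Trying to reproduce 17.** For two proportions pwr uses h = 2·arcsin(√p1) − 2·arcsin(√p2), with n per arm = 2·((1.960 + 0.842)/h)². For n = 17, h must be 2.802/√8.5 = 0.961.

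| Rates entered | h | n per arm |
|---|---|---|
| 25% v 12.5% (1/4 and 1/8 as proportions; a guess at what was entered) | 0.324 | 149.1, so 150 |
| 25% v 0% | 1.047 | 14.3, so 15 |
| 25.2% v 0.2% | 0.962 | 16.95, so 17 |
| 26% v 1% | 0.870 | 20.7, so 21 |
| 30% v 5% | 0.708 | 31.3, so 32 |
| 50% v 25% | 0.524 | 57.3, so 58 |

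With a 25-point difference, 17 appears only near 25.2% v 0.2%, or its mirror near 100%. These rates are not stated anywhere in the article.

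**2. Is the approximation sound there?** At 25% v 0% and 17 per arm, the arcsine formula gives power 0.86. The exact value can be worked by hand, because the experimental arm has no relapses:

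- Chi-square for 3 v 0 relapses is 34·(3·17)²/(3·31·17²) = 3.29, below 3.84. For 4 v 0 it is 4.53. So at least 4 control relapses are needed: P(X ≥ 4), X ~ Bin(17, 0.25), = 0.647.
- Fisher's two-sided p for 4 v 0 is 0.103, and for 5 v 0 it is 0.044. So at least 5 are needed: P(X ≥ 5) = 0.426.
- Expected relapses average 17 × 0.25 = 4.25 in total, about 2.1 per arm. The fallback to Fisher's test would therefore normally apply.

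**3. Exact power over all control rates.** All 2×2 tables were enumerated, with control rate 25% to 100% in steps of 0.5 points and a difference of 25 points. Fisher's test is uncorrected, because the article does not give the formula of Overall's correction.

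| Two-sided 5% | 17 per arm | 20 per arm |
|---|---|---|
| Chi-square throughout | 33–65% | 33–77% |
| Chi-square, Fisher if an expected count ≤ 5 | 28–43% | 33–59% |

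The maxima are at the 25% v 0% end (or its mirror). The smallest n per arm with exact power of at least 0.80 is 21 (chi-square) or 31 (Fisher) at 25% v 0%, 32 or 39 at 30% v 5%, and 59 or 64 at 50% v 25%.

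**4. One-sided 5% variant.** Chi-square alone at 25% v 0% has exact power 0.836 at 17 per arm and 0.909 at 20. The full rule with uncorrected Fisher peaks at 0.47 and 0.59; with a more liberal mid-p fallback the peaks are 0.65 and 0.775.

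**5. Illustration with the Background's 20%.** A 25-point reduction from 20% is impossible. For 20% v 0%, uncorrected Fisher again needs 5 v 0, so power is P(X ≥ 5) = 0.242 for Bin(17, 0.20) and 0.370 for Bin(20, 0.20). The corresponding chi-square values are 0.451 and 0.589.

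**The case against.** **Alpha and sidedness are unstated, so a test with 0.80 power might exist.** This stands in part. A reader might infer that 0.80 is out of reach on every reading, but the documents do not support that: a one-sided 5% plain chi-square exceeds 0.80 near 25% v 0%. It does not rescue the claim. A chi-square on a 2×2 table is ordinarily two-sided, the plan would normally use Fisher's test at those rates, and the full rule with uncorrected Fisher stays below 0.80 one-sided as well.

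**The fallback test was not computed as named.** Correct. The Fisher figures omit Overall's correction and cannot be quoted as the power of the planned test. The conclusion can still be bounded. To reach 0.80 at 25% v 0% with 20 per arm, a test would have to reject at 3 v 0 relapses. Even the uncorrected two-sided chi-square does not do so (40·(3·20)²/(3·37·20²) = 3.24, below 3.84).

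**The Background's 20% is not a design input.** Correct. It is an approximate two-year figure from cited studies, while treatment here lasts 12 months and relapse is defined from weekly PANSS ratings. A reader might take 20% as the control rate the trial assumed; the article never says so. It serves only as an illustration, and the conclusion does not depend on it.

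**A journal article may leave the control rate, alpha and the pwr function to a fuller protocol.** Also fair, and their absence is not the point. The point is that the figure the article does state fails for every control rate under the conventional test.

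**Conclusion.** The point holds at two-sided 5%. Even with NNT = 4 granted as the direct between-arm effect, no control relapse rate gives 0.80: the best case is 65% at 17 per arm and 77% with all 40 analysed. Both belong to a plain chi-square at 25% v 0% (or its mirror), where the plan's own rule would normally call for Fisher's test (43% and 59%, uncorrected). The figure of 17 may have come from the arcsine approximation with almost no relapses in the combined arm. That would explain the number but does not support 0.80 for the planned tests.

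The result rests on three assumptions: two-sided 5%, the 25-point reading of NNT = 4 (which favours the plan), and uncorrected Fisher in the fallback. As the sole support for the sample size on the primary outcome, the statement needs correcting.

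**What to change.** In Number of Participants and Power Analysis, remove or restate the 0.80 claim. State the assumed relapse rate in each arm, alpha and sidedness. Give exact power at 17 and at 20 per arm for the planned test, including its named correction, and label any uncorrected Fisher figures as such. If 20% v 0% is shown as an illustration, keep it apart from the figures for a 25-point difference. Keep enrolment at 40, do not describe the trial as having 0.80 power, and do not supply a rationale for 40 that the article does not contain.

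The cost is one reworded paragraph and a less favourable stated power. No extra patients are needed.
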